#### 7.1.2 Administration

**Initial practice assessments*.*** Initial practice assessments will be conducted prior to intervention implementation. An ***on-site practice champion*** identified by the practice will work with the investigative team to champion the intervention and its continued implementation and use, and ensure completion of all study assessments. The practice champion may be a physician, pharmacist, office manager, nurse, or other personnel.

Practice assessments will typically involve 2-3 meetings of about 30-60 minutes each, during which the investigative team will gather information regarding the practice’s motivation, resources, facilitators to conducting AWVs, current practice workflows and templates for AWVs, preferred workflows, and opportunities for change. Assessments will be performed via Zoom video conferencing, which have proven effective and efficient for intervention implementation and data collection across multiple sites,[^161^](#_ENREF_161) and enhances the potential for future widespread intervention dissemination. The study team will use information from the assessments to develop a prototype workflow, which they will present to the practice for discussion and revision. The investigators will also assess practice interest in using the resources available for download on the study website, introduce the website, and provide practices with the materials desired, as well as the website link so that they can browse, download, and use other desired resources. Discussions also will focus on selecting and tailoring EHR-based tools for their practice.

**Intervention implementation*.*** Once initial practice assessments have been completed, the practices have developed a workflow for conducting AWVs, and have selected their desired tools, the intervention will be implemented over 6 months. Intervention implementation will consist of “turning on” selected EHR-based tools, providing access to selected documentation and other templates, and training practice members on the use of these tools. Practice training sessions will occur during this period on the established practice-specific AWV workflow, benefits of AWVs, documentation requirements, services that clinicians can perform with the AWV without incurring extra patient costs, and potential billing strategies. The research team will interface with the practice champion regularly (on average likely about once every 1-2 months based on our experiences with our pilot practices) during the 6-month implementation period to identify and remedy barriers to implementation.

The investigative team will collate information from all sites on strategies for increasing AWVs and overcoming barriers to conducting AWVs and will share pertinent insights in a quarterly newsletter for practices that have already started intervention implementation. Practices will receive feedback reports on their AWV and preventive health services completion rates starting about 4-6 months after they begin intervention implementation until 12 months post-implementation. Practices will determine the desired frequency of these reports, which can be provided monthly to quarterly.

### 7.2 Fidelity

#### 7.2.1 Interventionist Training and Tracking

Variability of intervention implementation is expected because the intervention will be tailored by site. We will track dates of completion of meetings and trainings.

### 7.3 Measures to Minimize Bias: Randomization and Blinding

The study statistician will use stratified randomization to assign the order and timing of intervention implementation in practices. Stratification will be by organization to ensure that each cluster contains two practices from each organization. Randomization within each strata will be by simple randomization.[^162^](#_ENREF_162) Randomization will be performed before any practices are engaged in intervention implementation activities. Blinding procedures are not applicable for this study.

### 7.4 Study Intervention/Experimental Manipulation Adherence

The study team will assess and track details of all interactions with practices, including attendance at training sessions, and practice reports of use of intervention materials.

To remain an active participant in the study, practice facilitators must engage with and meet with the study team throughout the intervention implementation period.

### 7.5 Concomitant Therapy

Not applicable

#### 7.5.1 Rescue Therapy

Not applicable

## 8 STUDY INTERVENTION/EXPERIMENTAL MANIPULATION DISCONTINUATION AND PARTICIPANT DISCONTINUATION/ WITHDRAWAL

### 8.1 Discontinuation of Study Intervention/Experimental Manipulation

These are not applicable because the trial has low or negligible risk of meeting the usual criteria for stopping a study for safety, early success or futility. However, the trial may be stopped if external circumstances (including but not limited to national or global events) make continuation impossible. Reasons for discontinuation would be communicated to the NIH.

### 8.2 Participant Discontinuation/Withdrawal from the Study

Practices are free to withdraw from participation in the study at any time upon request. Practices that withdraw from the study will be replaced.

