### 6.7 Strategies for Recruitment and Retention

Healthcare organizations/practices will be recruited for the study. For the population cohort, there will be no direct patient recruitment. Outcomes will be extracted from EHRs and will not require active practice or patient participation. Patients will be recruited for one-time, semi-structured interviews. Clinicians and staff will be recruited for three sets of semi-structured interviews and clinicians for three sets of surveys. The interviews and surveys are not longitudinal and different clinicians/staff can participate at different time points. Retention strategies are not needed for this study.

Primary care practices. We have already obtained agreement for participation from 3 large organizations, each comprising at least 30-40 practice sites, and will select up to 8 from each organization to take part in this study.

Patients, clinicians, and staff will be recruited for semi-structured interviews. Clinicians will also be recruited for brief surveys. Informed consent for interviews and surveys will be provided by giving participants a study information sheet prior to the interview and/or obtaining oral consent.

*Patients* may be recruited in several ways:

- Identification of patients completing AWVs through EHR data extractions. The participating practice and/or a proxy designated by the practice (the DARTNet Institute or UCLA) will email or mail potential eligible patients a one-time recruitment letter and information sheet describing the study. Patients will be given the opportunity to phone or email the study team to opt-out of the study. A minimum of 1 week after the letter is sent, a study team member will telephone patients who do not opt-out for follow-up. Patients will receive up to 7 follow-up calls and/or emails, at least 1 week apart, up to 16 weeks after the letters are sent. Inquiries will be handled by the study team.
- Office staff and/or clinicians will invite patients to participate after they complete an AWV, by handing them an information flyer describing the interviews. The flyer will be used as the recruitment script.
- Office staff and/or clinicians will identify patients who previously completed an AWV and will invite them to participate in the study.

*Clinicians / staff*

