#### 10.4.2 Analysis of the Primary Endpoints

The primary endpoints are AWV utilization and the composite preventive health services score **(Table 6)**.

| **Table 6. Patient cohorts, primary endpoints, and timing of measurement** | | |
| --- | --- | --- |
| **Cohort** | **Endpoints** | **Time Frame** |
| Medicare patients aged 50+, with 1 or more visits in the past 12 months, not deceased | 1) ***AWV utilization*** (% of patients who completed an AWV or IPPE (CPT codes G0438, G0439, G0402)) within 12 months; 2) ***Composite preventive health services score*** (% of recommended services that are up to date) | Monthly |

***Primary objectives (examine effect of PT-AWV intervention on increasing AWVs and preventive health services utilization in diverse practice settings at 12, 18 and 24 months post-implementation)*:** we will use **linear mixed effects models** to assess the effect of the intervention on the use of AWVs and on the composite preventive health services score. These models account for correlation between repeated observations in the same cluster and the confounding effects of time and treatment. For example, with $Y_{ijt}$ as the indicator of AWV completion for patient i from cluster j at time t, the model is:

$Y_{ijt}=\mu+\alpha_{i}+\gamma_{j}{+ \beta}_{t}+X_{ijt}\theta+ Z_{ijt} + \varepsilon_{ijt}$,

where $\mu$ is the intercept,$\gamma_{i}$ and $\alpha_{j}$ are the random intercepts for subject i and cluster j with $\alpha_{j}\sim N\left( 0, \sigma_{\alpha}^{2} \right), \gamma_{j}\sim N\left( 0, \sigma_{\gamma}^{2} \right),$ $\beta_{t}$ is the fixed time effect, $X_{ijt}$ is the indicator of treatment mode for subject i cluster j at month t, $\theta$ represents the treatment effect, $Z_{ijt}$ is pre-specified patient and practice level covariate, and $\varepsilon_{ijt}$ is the residual with $\varepsilon_{ijt}\sim N\left( 0, \sigma_{\varepsilon}^{2} \right)$. We will approximate the secular time trend $\beta_{t}$ linearly in time with $\beta t$. Piece-wise constant time effect will be considered to accommodate possible non-linear time trends. This model will accommodate repeated patient visits and correlations within practices. All analyses will be carried out based on the intention to treat principle, which means that the treatment mode variable ($X_{ijt})$ is determined by the scheduled assignment of intervention implementation based on randomization, but not by the actual timing of implementation.

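### Section 8.2 replaces practices that withdraw after randomisation, which conflicts with the intention-to-treat rule and does not secure withdrawn practices a place in the analysis

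*Protocol*

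**What the plan says.** - **Randomisation (Protocol 7.3).** The statistician assigns order and timing, stratified by organisation. "Randomization will be performed before any practices are engaged in intervention implementation activities". Also: "Stratification will be by organization to ensure that each cluster contains two practices from each organization".
- **Withdrawal (Protocol 8.2).** "Practices are free to withdraw from participation in the study at any time upon request". The next sentence is: "Practices that withdraw from the study will be replaced". No time limit, no rule for the replacement's step and no rule for the leaver's data are given.
- **Adherence (Protocol 7.4).** "To remain an active participant in the study, practice facilitators must engage with and meet with the study team throughout the intervention implementation period".
- **Analysis (Protocol 10.4.2).** "All analyses will be carried out based on the intention to treat principle". The same sentence explains that the treatment indicator comes from the randomised schedule and not from when implementation actually happened.
- **Outcome data (Protocol 6.7).** "Outcomes will be extracted from EHRs and will not require active practice or patient participation".

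**The concern.** Randomisation precedes implementation, so any practice that withdraws during or after implementation does so as a randomised unit. Section 8.2 is a stated rule, and as written it lets a practice that was never randomised take that unit's place. The newcomer is picked after randomisation and is, by construction, willing to join at that point.

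Two things are at stake. First, the exposure rule in 10.4.2 cannot be applied to a practice without a randomised schedule. Second, if practices that struggle with the intervention are more likely to leave, and their data are not analysed, poor results drop out of the estimate. That matters most for sustainability, which the synopsis puts first in the overall goal. With 6 practices per step, one replacement is 1/6 = 17% of a step.

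**Working it through.** **1. Sections 8.2 and 10.4.2 side by side.** The protocol describes no reserve practices randomised in advance. A post-randomisation replacement can then receive a step in one of two ways:

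- *It gets its own start date.* Its treatment indicator is not set by randomisation, contrary to 10.4.2.
- *It inherits the vacated slot.* Step balance survives if it comes from the same organisation. It is still a unit selected after randomisation, and if the slot's date has passed, months are coded as exposed when the practice had no exposure. That second error would dilute the effect, so the bias need not always be upward.

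In neither case does any sentence say that the withdrawn practice is also analysed.

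**2. Does the power case need replacement?** Inputs from 10.2 and 5.1: 24 practices, 4 steps of 6, α = 0.05 (two-sided assumed), 800 to 1,500 patients per practice, ICC 0.03 and 0.05, an increase of 10 (read as percentage points), baselines 10, 30 and 50%. Method: the Hussey-Hughes variance for a cross-sectional stepped wedge with T = 5 periods,

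Var = Iσ²(σ² + Tτ²) / [(IU − W)σ² + (U² + ITU − TW − IV)τ²],

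with I = 24, U = 6(4+3+2+1) = 60, V = 6(16+9+4+1) = 180 and W = 0+36+144+324+576 = 1,080. The brackets become 360σ² + 1,080τ².

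Least favourable Table 4 AWV cell (baseline 50%, 800 patients, ICC 0.03):
- total variance at the midpoint rate = 0.55 × 0.45 = 0.2475
- τ² = 0.03 × 0.2475 = 0.007425
- σ² = 0.97 × 0.2475 / 800 = 0.000300
- Var = 24 × 0.000300 × (0.000300 + 0.037125) / (0.108 + 8.019) = 0.0000332
- SE = 0.0058 and 0.10 / 0.0058 ≈ 17, so power is above 99%.

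This reproduces the plan's figure; SEs across the AWV cells run from 0.003 to 0.006. With 18 practices spread evenly over the steps, the SE rises by √(24/18) = 1.155 to about 0.0067, and 0.10 / 0.0067 ≈ 15. Power is still above 99%.

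**3. Illustration of size (assumptions, not protocol figures).** Suppose k of 24 practices leave with zero effect, all others, including replacements, gain 10 points, and leavers' data are not analysed. The effect with all practices kept as randomised is 10 × (24 − k)/24.

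| k leaving | Kept as randomised, by formula | Kept as randomised, simulated | With replacement, simulated | Overstatement by formula |
| --- | --- | --- | --- | --- |
| 2 | 9.2 | 9.1 | 10.0 | 0.8 points (10/9.17 − 1 = 9%) |
| 4 | 8.3 | 8.3 | 10.0 | 1.7 points (10/8.33 − 1 = 20%) |
| 6 | 7.5 | 7.5 | 10.0 | 2.5 points (10/7.5 − 1 = 33%) |

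The simulation used practice-period means, a random practice intercept, fixed period effects, baseline 30%, ICC 0.05, 1,300 patients per practice-period and 1,000 runs.

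**4. False positives under no effect.** In the same set-up, 2 to 6 practices from the first two steps were replaced by practices placed in the last step.
- Equal secular trends: no bias, rejection rate 4 to 6%.
- Replacements' trend differing by 1 point per period: bias 0.1 to 0.3 points in either direction, rejection rate 6 to 11%.

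The simulation error on a 5% rate is √(0.05 × 0.95/1,000) = 0.7 points, so only the upper part of that last range is clearly above 5%.

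**The case against.** The best defence is that 8.2 is silent on analysis. Adding a practice to restore the count is compatible with analysing the leaver as randomised, and 10.4.2 states intention to treat for all analyses. The detail could sit in the SAP, which is not at hand. This stands in part: the protocol nowhere says that leavers' data are discarded. It does not remove the conflict, because the replacement itself has no randomised schedule and 8.2 puts no time limit on replacement.

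Two stronger readings are tempting, and the documents do not support them.

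- *A practice that stops engaging is swapped out.* Section 7.4 makes engagement a condition of active status: "practice facilitators must engage with and meet with the study team throughout the intervention implementation period". It does not mention removal, replacement or exclusion from analysis. Section 8.2 concerns withdrawal on request. The link between the two is inference.
- *The randomised order is necessarily broken.* Section 8.2 does not say which step a replacement takes. Section 6.7 describes organisations with at least 30 to 40 sites, so a same-organisation replacement in the vacated slot is feasible and would keep step balance.

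It is also fair to object that the illustration builds in its answer. It assumes zero effect in every leaver, the full gain in every replacement and leavers' data left out. A practice might leave for unrelated reasons or before implementation starts. Finally, EHR extraction needs no active participation, but section 11.8.1 makes data sharing depend on data use agreements, so a full withdrawal could end access.

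**Conclusion.** The point holds in limited form. Section 8.2 permits an unrandomised practice, selected after randomisation, to take the place of a randomised one. That conflicts with the exposure rule in 10.4.2, and the protocol does not secure the leaver's place in the analysis.

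The size is unknown. An overstatement of 0.8 to 1.7 points on a 10-point effect follows only if 2 to 4 practices leave with zero effect, replacements gain the full 10 points and leavers' data are not analysed. A reader might take the corresponding 9 to 20% as an expected inflation; nothing in the documents supports a withdrawal count or a reason for leaving. At these sizes, with power above 99%, whether an effect is detected would be unlikely to change. What is exposed is the size of the effect and the claim that it lasts. The change is worth making because it is cheap and power does not depend on replacement.

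**What to change.** - **Section 8.2.** Keep every randomised practice in the primary analysis at its scheduled step. Continue EHR extraction after a practice stops intervention activities, unless data access under the data use agreement is revoked. Allow replacement only before randomisation, or from reserve practices randomised in advance within each organisation. Report any other later addition in a sensitivity analysis only.
- **Section 7.4.** Add that active participant status does not affect inclusion in the analysis.
- **Data use agreements.** Add a line providing for continued extraction after withdrawal from intervention activities.

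The cost is this wording and possibly a smaller effect estimate. It is best settled before any practice withdraws, since outcome data not extracted at the time may not be recoverable later.

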### 8.3 Lost to Follow-up

Not applicable

## 9 STUDY ASSESSMENTS AND PROCEDURES

### 9.1 Screening Procedures

**9.1.1 Screening activities performed prior to obtaining informed consent**

Minimal risk activities that may be performed before a participant has provided oral informed consent or has been given an information sheet regarding semi-structured interviews include the following:

- EHR data extractions to identify a list of eligible participants.
- Email, written, in person or telephone communications with prospective subjects.

**9.1.2 Screening activities performed after a consent for screening has been obtained**

Not applicable

### 9.2 Study Evaluations & Procedures

*EHR data extractions to identify patients for interviews* will be performed to identify eligible patients for semi-structured interviews. Information obtained through the extractions will include patient names, contact information, and date of birth. Extractions will occur within about 1-6 months prior to patient participation in interviews. Clinicians/staff will be identified by practices for participation.

*Clinician/staff interviews* will be conducted via telephone or Zoom videoconferencing and will last approximately 30 minutes. Interviews will be audio-recorded and transcribed verbatim for analysis. Interviews are not longitudinal. Different clinicians/staff may participate at different time points. Interviews will be conducted by a team member with qualitative research expertise.

*Patient interviews* will be conducted via telephone and will last approximately 45-60 minutes. These one-time interviews will be audio-recorded and transcribed verbatim for analysis. Interviews will be conducted by a team member with qualitative research expertise.

*Clinician surveys* will be administered via REDCap or Qualtrics, and will take approximately 5-10 minutes or less to complete. Clinicians will be identified by practice leads for participation.

*Data extractions to assess primary and secondary outcomes*. The DARTNet Institute will serve as the data coordinating center for this study. Organizations will either send DARTNet limited datasets for standardization, or DARTNet will work with the institutions to extract the requisite data to assess study outcomes, which include completion of AWVs and the preventive health measures depicted in [**Section 4**](#_4_OBJECTIVES_AND) (**Table 2**). [name] (co-investigator) will process data and clean the data, help create analytic datasets, and will transfer limited datasets to UCLA for analysis. Data will be extracted at baseline and in July 2025, July 2026, and July 2027.

#### 9.2.1 Biospecimen Evaluations

Not applicable

#### 9.2.2 Samples for Genetic/Genomic Analysis

##### 9.2.2.1 Description of the scope of genetic/genomic analysis

Not applicable

##### 9.2.2.2 Description of how privacy and confidentiality of medical information/biological specimens will be maximized

Not applicable

##### 9.2.2.3 Management of Results

Not applicable

##### 9.2.2.4 Genetic counseling

Not applicable

### 9.3 Safety Assessments

Not applicable

### 9.4 Adverse Events and Serious Adverse Events

#### 9.4.1 Definition of Adverse Event

Adverse events are not anticipated because the intervention is performed at the level of the practice, and not with patients. The risks of the study are minimal as the intervention promotes practices that are part of routine clinical care.

Adverse event means any untoward medical occurrence associated with the use of an intervention in humans, whether or not considered intervention-related (21 CFR 312.32 (a)).

#### 9.4.2 Definition of Serious Adverse Events (SAE)

An adverse event (AE) or suspected adverse reaction is considered "serious" if, in the view of either the investigator or sponsor, it results in any of the following outcomes: death, a life-threatening adverse event, inpatient hospitalization or prolongation of existing hospitalization, a persistent or significant incapacity or substantial disruption of the ability to conduct normal life functions, or a congenital anomaly/birth defect. Important medical events that may not result in death, be life-threatening, or require hospitalization may be considered serious when, based upon appropriate medical judgment, they may jeopardize the participant and may require medical or surgical intervention to prevent one of the outcomes listed in this definition. Examples of such medical events include allergic bronchospasm requiring intensive treatment in an emergency room or at home, blood dyscrasias or convulsions that do not result in inpatient hospitalization, or the development of drug dependency or drug abuse.

#### 9.4.3 Classification of an Adverse Event

##### 9.4.3.1 Severity of Event

For adverse events (AEs) not included in the protocol defined grading system, the following guidelines will be used to describe severity.

- **Mild** – Events require minimal or no treatment and do not interfere with the participant’s daily activities.
- **Moderate** – Events result in a low level of inconvenience or concern with the therapeutic measures. Moderate events may cause some interference with functioning.
- **Severe** – Events interrupt a participant’s usual daily activity and may require systemic drug therapy or other treatment. Severe events are usually potentially life-threatening or incapacitating. Of note, the term “severe” does not necessarily equate to “serious”.

